## Abstract

**Background:**

In the absence of disease-modifying interventions for hand osteoarthritis (OA), occupational therapy (OT) comprising patient education, hand exercises, assistive devices and orthoses are considered as core treatments, whereas surgery are recommended for those with severe carpometacarpal (CMC1) OA. However, even though CMC1 surgery may reduce pain and improve function, the risk of adverse effects is high, and randomized controlled trials comparing surgery with non-surgical interventions are warranted.

This multicentre randomized controlled trial aims to address the following questions:

Does OT in the period before surgical consultation reduce the need for surgery in CMC1-OA?

What are patients’ motivation and reasons for wanting CMC1-surgery?

Are there differences between departments of rheumatology concerning the degree of CMC1-OA, pain and functional limitations in patients who are referred for surgical consultation for CMC1 surgery?

Is the Measure of Activity Performance of the Hand a reliable measure in patients with CMC1-OA?

Do patients with CMC1-OA with and without affection of the distal and proximal interphalangeal finger joints differ with regard to symptoms and function?

Do the degree of CMC1-OA, symptoms and functional limitations significantly predict improvement after 2 years following OT or CMC1-surgery?

Is OT more cost-effective than surgery in the management of CMC1-OA?

**Methods/Design:**

All persons referred for surgical consultation due to their CMC1-OA at one of three Norwegian departments of rheumatology are invited to participate. Those who agree attend a clinical assessment and report their symptoms, function and motivation for surgery in validated outcome measures, before they are randomly selected to receive OT in the period before surgical consultation (estimated *n* = 180). The primary outcome will be the number of participants in each group who have received surgical treatment after 2 years. Secondary and tertiary outcomes are pain, function and satisfaction with care over the 2-year trial period. Outcomes will be collected at baseline, 4, 18 and 24 months. The main analysis will be on an intention-to-treat basis, using logistic regression, comparing the number of participants in each group who have received surgical treatment after 2 years.

**Discussion:**

The findings will improve the evidence-based management of HOA.

**Trial registration identifier:**

NCT01794754. First registrated February 15^th^ 2013.

## Background

Hand osteoarthritis (HOA) is one of the most common joint conditions, especially in women, and has an increasing prevalence due to the ageing of the population [1]. Clinical manifestations are soft-tissue swelling and bony enlargements, most frequently in the distal and proximal interphalangeal finger joints, and of the carpometacarpal (CMC1) joint of the thumb [2]. Symptoms and functional consequences include pain, stiffness, reduced grip strength and hand function, and impaired activity performance and quality of life [3, 4]. In a recent study examining the consequences of HOA, the results also showed a substantial and similar impact on work productivity across five European countries [5].

Studies further indicate that people with CMC1-OA have more severe pain and disability than those without involvement of this joint [6, 7]. The prevalence of CMC1-OA has been estimated at 13% in people aged 41 to 50 years, increasing to 68% in people between 71 and 80 years of age [8]. In the absence of disease-modifying interventions, non-pharmacological approaches such as patient education, hand exercises, assistive devices and orthoses for the CMC1-joint are considered as core treatments for HOA, while surgery is recommended for those with severe CMC1-OA [1, 9, 10]. The non-pharmacological interventions for HOA are most frequently delivered by occupational therapists [11], and research supports that these interventions are safe and effective [12–14].

In Norway, the Directorate of Health has assigned the main responsibility for OA care to the primary health care services [15]. Recent research indicates, however, that the quality of these services in general is sub-optimal [16], and that especially people with HOA have poor access to recommended treatment both in primary and secondary care [17, 18]. While persons with hip or knee-OA often receive physiotherapy, few with HOA have seen an occupational therapist [19, 20]. Thus, the care of people with HOA is most frequently limited to general practitioner (GP) consultations, while those with severe CMC1-OA may be referred for surgical consultation. The waiting time for surgical consultation in Norway is usually between three and 6 months, followed by a waiting period of 6 to 12 months prior to surgical treatment.

### Surgery for carpometacarpal osteoarthritis

CMC1-OA presents with a combination of reduced cartilage thickness, increased ligament laxity with resultant instability, and subluxation of the base of the metacarp on the trapezium, which in turn results in adduction contracture and decreased thumb web space [21]. As the severity of symptoms does not necessarily correspond with the radiographic stage of the disease, the main indications for surgery are pain and loss of function [22]. Surgical procedures most frequently comprise trapeziectomy with or without ligament reconstruction and tendon interposition (LRTI), and in the most severe cases trapeziometacarpal arthrodesis. Two systematic reviews comparing the effect of different surgical techniques in CMC1-OA conclude that there is currently no evidence that one surgical procedure is superior to another [23, 24]. The results further show that 10% of the participants who underwent trapeziectomy and 22% who underwent trapeziectomy with LRTI had adverse effects, including scar tenderness, tendon adhesion or rupture, sensory change, or complex regional pain syndrome [23]. Complications and repeat surgeries were also frequently reported following CMC1 arthrodesis, with non-union rates between 8 and 21% [24]. A recent randomized controlled trial (RCT), comparing arthrodesis with trapeziectomy with LRTI, was prematurely terminated due to the high prevalence of complications: 71% in the arthrodesis group and 21% in the trapeziectomy with LRTI group [25]. Thus, even if CMC1 surgery may reduce pain and improve function, the risk of adverse effects is high, and RCTs comparing surgery with non-surgical interventions are warranted. In a recent review of surgery for thumb osteoarthritis, the authors did not identify any studies that compared surgery to sham surgery or to non-operative treatments [26]. However, in a small prospective study evaluating the effect of occupational therapy (assistive devices alone or with addition of one of two types of orthoses) for patients awaiting CMC1-surgery, 23 out of 33 participants (70%) no longer required an operation after 7 months, while only two of the remaining 19 participants wanted an operation after 7 years [27]. The results thereby indicate that occupational therapy may reduce the need for surgery. However, as this was a small study with a high risk of bias, robust RTCs comparing the effects of occupational therapy and surgery are needed.

### Occupational therapy for hand osteoarthritis

Occupational therapy aims at enhancing activity, participation and health-related quality of life. Interventions in occupational therapy for HOA most frequently comprises patient education, hand exercises, and the provision of assistive devices and thumb orthoses [28].

### Patient education

Based on one RCT [29], the authors of a review of treatment for HOA conclude that educating patients about self-management is effective for alleviating pain and avoiding disability [14]. In two later studies, the authors of a Dutch RCT found no effectiveness of a group-based multidisciplinary treatment programme [30], while there was a significant improvement in pain self-efficacy and a higher proportion of people meeting the OARSI responder criteria [31] among those receiving patient education (joint protection) compared to those who did not in a recent British RCT [32]. Further, participants in qualitative studies report that they experience lack of help, and little and/or contradictory information with regard to management of their condition [18, 19]. Thus, there is a need for developing education material that is unique to HOA and based on high-quality published evidence for HOA treatments.

### Assistive devices

Results from an RCT demonstrated that use of assistive devices significantly improved activity performance and satisfaction with performance in patients with HOA [33]. In addition, the use of assistive devices was the most frequently reported self-management strategy in a study exploring self-management strategies in persons with HOA [34]. Furthermore, participants with HOA have reported in qualitative interviews that assistive devices help them remain independent in daily activities [18, 19]. However, despite the availability of such devices, the participants had seldom received any information or guidance from health professionals during the process of selecting appropriate devices.

### Hand exercises

Several systematic reviews conclude that there is some, although limited, evidence that hand exercises may reduce pain and increase joint mobility and grip strength in HOA [12–14, 35, 36]. Furthermore, there were no differences among those who received the multidisciplinary programme that included hand exercises compared to those who did not receive this programme in a recent Dutch RCT [30], or between the groups that received hand exercises versus those who did not in a British RCT [32]. However, none of these interventions included monitoring during the study period, and the rationale for the design of the exercise programmes is unclear. Moreover, when comparing the cost-utility of joint protection only, hand exercises only, and joint protection plus hand exercises with leaflet and advice (control group) in the British study, the findings showed that hand exercises was the most cost-effective option [37].

In a recent Norwegian RCT, hand exercises led to significant and clinically important functional improvements in terms of decreased pain and fatigue, increased thumb web space, approximately 25% improvement in grip strength, and improved activity performance [38]. The selection and monitoring of exercises in the study was in accordance with recent research and recommendations for exercises for HOA in general [1, 13, 39], as well as for CMC1-OA [21, 40–42]. As the intervention was well tolerated and delivered at a low cost with respect to time expended and exercise materials used, the authors conclude that the programme should be considered for inclusion in the standard care for people with HOA [38]. In another Norwegian study investigating the effect of the same exercise programme, but with three additional exercises for the shoulder girdle and upper arm, these findings were supported, although the effects were more limited [43]. It therefore seems that the less comprehensive programme may be easier to perform on a regular basis, thus making it probably the most effective.

### Thumb orthoses

Based on the best available evidence, the European League Against Rheumatism (EULAR) recommends that persons with CMC1-OA should be provided with orthoses to prevent or correct subluxation and deformity of the thumb [1]. The effect of CMC1 orthoses has been addressed in six systematic reviews [1, 12, 13, 35, 36, 44]. Based on a meta-analysis of two randomized controlled trials, the authors in one of the most recent reviews conclude that there is consistent evidence that orthoses reduce hand pain [13]. The results from single trials included in this review further indicate that subluxation was reduced when wearing orthoses and more reduced with a rigid orthosis than with a soft one [45]. In the two included studies with a low risk of bias, a long and rigid orthosis was found to be pain relieving and well tolerated for long-term night use [46], while a shorter orthosis used during activities of daily living significantly reduced pain [47]. An effective regimen may therefore be a combination of a small and rigid orthosis for pain relief during the day and a rigid nighttime orthosis for prevention of deformities.

### Functional assessment of hand osteoarthritis

Appropriate outcome measures, based on patients’ concerns, are necessary for the comprehensive evaluation of existing and new interventions in HOA [48]. Such instruments should also be feasible, valid, reliable, and responsive to change. Currently, two patient reported outcomes (PROs) have been developed specifically for HOA: the Australian/Canadian Hand Osteoarthritis Index (AUSCAN) [49] and the Functional Index of HOA (FIHOA) [50]. In a Norwegian study comparing the psychometric properties of these measures, the results indicated that both of these questionnaires contained items that were deemed irrelevant by the Norwegian respondents, such as gender-specific questions and items addressing activities that are not relevant in a Norwegian context [51]. The items are further limited to activities within self-care and house work, and do not include any questions related to activities within work or leisure. The Measure of Activity Performance of the Hand (MAP-Hand) is a PRO where the items were generated through interviews with people with arthritis [52]. In addition to 18 standardized items, the questionnaire includes five open questions, where patients can add other activities of importance to daily functioning. This provides clinicians with important information for goal-setting processes, planning and evaluation of interventions, and meet the need for outcome measures that incorporate the patient perspective as stated by the Outcome Measures in Rheumatology Group (OMERACT) [48]. MAP-Hand has been tested for validity and responsiveness in rheumatoid arthritis (RA) and HOA with good results, but studies of reliability, including estimating the smallest detectable difference and minimal important change are warranted [53].

## Methods/Design

### Aims and research questions

The main objective will be to evaluate whether occupational therapy reduces or delays the need for surgery in carpometacarpal osteoarthritis during the waiting period prior to surgical consultation.

More specifically, our study will consider the following research questions:Does occupational therapy in the period before surgical consultation reduce the need for surgery in CMC1-OA (reduces the proportion of patients who receives CMC1-surgery)?What is the patients’ motivation and what reasons are given for wanting CMC1-surgery?Are there differences between departments of rheumatology with regard to degree of CMC1-OA, pain and functional limitations in patients referred for surgical consultation for CMC1 surgery?Is the Measure of Activity Performance of the Hand (MAP-Hand) a reliable measure in patients with CMC1-OA?Do patients with CMC1-OA with and without affection of the distal and proximal interphalangeal finger joints differ with regard to symptoms and function?Do the degrees of CMC1-OA, symptoms and functional limitations significantly predict improvement after 2 years following occupational therapy or CMC1-surgery?Is occupational therapy more cost-effective than surgery in the management of CMC1-OA?

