### Study design and setting

This is a Norwegian multicentre randomized controlled trial (Trial registration: NCT01794754). The trial will be conducted at the departments of rheumatology at St. Olav’s Hospital, Trondheim University Hospital in Trondheim, Haukeland University Hospital in Bergen and Haugesund Rheumatism Hospital in Haugesund, in collaboration with the National advisory unit on rehabilitation in rheumatology, which is located at Diakonhjemmet Hospital in Oslo. Participants will be allocated to receive either standard care (no intervention) or occupational therapy during the waiting period between referral for and the actual surgical consultation (see Fig. 1). The occupational therapy intervention represents a supplement to standard HOA care, and no participant will receive an intervention that is below the current standard of care.

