### Data collection

Participant flow is shown in Fig. 1. Follow-up will be at 4 months (immediately before the surgical consultation), 18 months and 24 months after randomization to evaluate short, medium and long-term effects. Before each follow-up, a questionnaire will be sent to the participants, who will be asked to fill it in at home and bring it to the follow-up appointment.

Additionally, participants in the control group will receive a phone call 2 weeks after baseline assessments, and will complete the MAP-Hand in a telephone interview. Participants in the intervention group will be convened for a second consultation 2 weeks after baseline, at which time the orthoses and the hand exercise programme will be adjusted, and additional information regarding use of assistive devices will be given if needed.

The surgical consultation takes place immediately after the follow-up assessment at 4 months. Based on the patient’s symptoms, functional limitations and degree of CMC1-OA, the surgeon may reach one of the three following conclusions;the patient is not eligible for surgery, and will need a new referral from his/her GP to be scheduled for a new surgical consultationthe patient is scheduled for a new surgical consultation after 6 to 12 months, due to uncertainty related to eligibility, orthe patient is eligible for surgery and will receive an appointment for operation, (usually after 6 to 10 months on a waiting list).

All participants who are operated on, regardless of group affiliation, will be given post-operative treatment according to surgical procedures and recommendations.

The third and fourth follow-up will be after 18 and 24 months, respectively. Baseline assessments will be repeated, and for participants in the occupational therapy group, exercises and orthoses will be adjusted if needed. Participants in the control group will receive the occupational therapy intervention after assessments at the control at 24 months.

Each participant will have a special numeric code, and all data will be stored in a fireproof and locked cupboard and in a digital file on the research server at Diakonhjemmet Hospital. Selected members of the project group (project leader, local coordinators, bio-statistician, study assistants, a PhD-student and a post doc research fellow) can access the file. The OT will check missing data in the questionnaires at each follow-up. An independent study assistant will check incorrect and double data entries.

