To assess the cost-effectiveness, we will need to estimate health outcomes and costs. The health outcomes will be measured using the EQ-5D and the costs will include the cost of the two interventions. This comprises the hours and frequency of occupational therapy, costs related to the provision of assistive devices, orthoses, and exercise material, and costs related to the surgical procedures, including post-operative treatment. Furthermore, costs related to medical or technical equipment purchased by participants and to the use of other health care services (home care services, rehabilitation, and institution) will be recorded for both the intervention and control group during the trial period.

Standard methods for economic evaluation will be applied and the cost-effectiveness will be calculated as the incremental cost-effectiveness ratio, which is defined by the cost per incremental QALY.

The level of significance will be set to 0.05 and we will use IBM SPSS Statistics 21 (IBM Corporation), R (R Core Team (2016). R: A language and environment for statistical computing. R Foundation for Statistical Computing, Vienna, Austria.) and Statistical Analysis System (SAS Institute Inc., Cary, NC, USA).

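### Research question 7 asks whether occupational therapy is more cost-effective than surgery, but surgery is an outcome of this trial and not a randomised comparator

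*Protocol article*

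**What the plan says.** The seventh research question, given in the Abstract and again under Aims and research questions, reads "Is occupational therapy more cost-effective than surgery in the management of CMC1-OA".

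Study design and setting describes the allocation: "Participants will be allocated to receive either standard care (no intervention) or occupational therapy during the waiting period". It adds that "The occupational therapy intervention represents a supplement to standard HOA care".

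Data collection places the surgical decision at the consultation that follows the 4-month assessment. There, on the patient's "symptoms, functional limitations and degree of CMC1-OA, the surgeon may reach one of the three following conclusions": not eligible, a new consultation later, or eligible and put on the waiting list. The section provides for surgery in both arms: "All participants who are operated on, regardless of group affiliation, will be given post-operative treatment".

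Statistical analyses then says of the economic evaluation: "The health outcomes will be measured using the EQ-5D and the costs will include the cost of the two interventions". The cost list that follows covers OT time, devices, orthoses and exercise material, and also "costs related to the surgical procedures, including post-operative treatment". The summary measure is an incremental cost-effectiveness ratio (ICER), expressed as cost per incremental QALY. The two groups it contrasts are not named. The intention-to-treat statement in the same section is made for the main treatment analysis.

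**The concern.** An ICER is a difference in cost divided by a difference in QALYs between two defined groups. Question 7 names those groups as OT and surgery. The design creates two others: OT before the consultation followed by whatever care is then needed, and standard care before the consultation followed by whatever care is then needed. Nobody is allocated to surgery, and nobody is allocated to OT in place of surgery.

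What is at stake is the meaning of the economic result. The Dissemination section plans at least seven articles and links the last four research questions to articles of their own, so question 7 is due to be published separately. The Discussion expects the economic evaluation to inform policymakers. A ratio reported under the heading of OT against surgery would be read as a randomised comparison of the two treatments, which this trial cannot provide.

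**Working it through.** **Question, design and analysis side by side**

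| Element | Protocol article | Consequence |
|---|---|---|
| Question 7 (Abstract; Aims and research questions) | OT against surgery | Surgery is treated as a comparator |
| Allocation (Study design and setting) | OT or standard care during the wait | Surgery is not an arm |
| Role of OT (Study design and setting) | Added to standard care | OT is not an alternative to surgery |
| Surgical decision (Data collection) | After randomisation, by the surgeon, on clinical status | Surgery follows indication |
| Who may be operated on (Data collection) | Participants in either group | Surgery costs arise in both arms |
| Primary outcome (Outcome measures) | Number operated on by 2 years | Surgery is the endpoint |
| Costs (Statistical analyses) | "the costs will include the cost of the two interventions" | The framing of question 7 is repeated |
| ICER (Statistical analyses) | Groups not named | The contrast is left open |

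**The two ways of calculating the ICER**

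1. *By treatment received.* This follows the words of question 7. The groups would be formed after randomisation, by a decision that depends on symptoms and function. Those features are closely tied to the quality of life that the EQ-5D measures, so the comparison is confounded by indication.
2. *By randomised arm.* Randomisation protects this comparison. It estimates the cost per QALY of adding OT before the consultation, with surgery as a downstream cost in both arms. It does not say whether OT is more cost-effective than surgery.

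The first route answers the question without the protection of randomisation. The second keeps that protection and answers another question.

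**How far the arms are from OT and surgery**

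Inputs from Sample size calculations: at least 70% operated, a 20-point difference (so 50% in the OT arm), 90 per arm, one-sided significance level 0.05, power 80%, dropout 20%.

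The stated sample size reproduces with the unpooled two-proportion formula:

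- n per arm = (1.645 + 0.842)² × (0.70 × 0.30 + 0.50 × 0.50) / 0.20² = 6.185 × 0.46 / 0.04 = 71.1, rounded up to 72
- 72 / (1 − 0.20) = 90 per arm, 180 in total

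That figure belongs to the primary outcome and is unaffected here. The same rates applied to 90 per arm, before dropout, give:

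- OT arm: 90 × 0.50 = 45 operated, 45 not
- Control arm: 90 × 0.70 = 63 operated, 27 not

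So half of the OT arm would have both OT and surgery, and 27/90 = 30% of controls would have neither. This is an illustration only. The 70% is stated for patients deemed eligible for surgery, whereas participants are randomised on referral, before a surgeon has judged eligibility. The 50% is the effect the trial is sized to detect, and is not a forecast. At any rates short of 100% in controls and 0% in the OT arm, the arms differ from OT and surgery.

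**The case against.** The strongest reply is that the article never says the ICER will be calculated by treatment received. A reader might infer such a plan from question 7, but the Statistical analyses section does not announce one. Its nearest statement on grouping points the other way: purchased equipment and other health care services are to be costed for both the intervention and the control group. The phrase about two interventions can also be read as a list of items to be costed wherever they occur. This stands. The confounded analysis is what the question calls for, not something the plan has committed to.

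A second reply is that naming the ICER groups is detail that an article may leave to a fuller plan. On its own that would be right. But the question itself is stated, twice, and it contradicts the stated design. A fuller plan that specified analysis by arm would leave that contradiction in place.

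Three further inferences are tempting and unsupported:

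- *That OT would look cheaper and more effective.* Patients who avoid surgery may be those doing better, which would favour OT. Operated patients may start with worse utility and have more room to improve, or regress to the mean, which would favour surgery. The direction is uncertain.
- *That the share of participants fitting neither side of an OT-against-surgery split measures the error.* It describes a grouping that the article does not specify.
- *That the question on predictors of improvement after OT or surgery has the same fault.* It is prognostic and does not pose an effect comparison between the two treatments.

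**Conclusion.** The point holds: question 7 is wrong as written. It uses the trial's primary outcome as a comparator, and the costing text repeats that framing. The trial can give a randomised answer on the cost-effectiveness of adding OT before the surgical consultation. It cannot give one on OT against surgery.

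Severity is moderate. This is a secondary economic question. The primary outcome, the main analysis and the sample size of 180 are untouched. No numerical bias can be attached, because the article fixes no analysis by treatment received and the direction of any confounding is unknown. The conclusion rests on the allocation and the surgical decision process as described, and does not depend on the assumed surgery rates.

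**What to change.** 1. In the Abstract and under Aims and research questions, reword question 7 along these lines: is adding occupational therapy before the surgical consultation cost-effective compared with the usual pathway to consultation and, where indicated, surgery?
2. In Statistical analyses, state that incremental costs and incremental QALYs are differences between the randomised arms by intention to treat. Count OT, surgical and post-operative costs in whichever arm they occur, and replace the reference to two interventions accordingly.
3. Label any comparison of OT with surgery by treatment received as observational, with no causal conclusion.

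The cost is wording only. The EQ-5D, treatment sessions, devices and orthoses, and health care use are already scheduled in Table 5. Operations are recorded in both arms as the primary outcome, and surgical and post-operative costs are already in the planned cost list. Controls are offered OT only after the 24-month assessment, so the comparison by arm is available over the whole trial period. The reworded question also fits the decision raised in the Discussion, which is whether OT should come before surgery is considered.
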